**Fig. 1 Fig1:**
[figure not shown]
Flux diagram and procedure

During follow-ups at 1 month and then at 6 months, alcohol-related questionnaires from the initial visit will be offered again online (LimeSurvey) to the 170 participants to allow for the longitudinal evaluation of these different measures. In addition, all students will be asked to answer regular questionnaires based on Ecological Momentary Assessment (EMA) on an offline mobile application in order to evaluate the monthly BD score (main criterion) and the weekly amount of alcohol consumed and to follow their mindfulness meditation practice (only for the experimental group). This data collection will be done between the different sessions (initial visit “T0” and follow-ups at 1 month “T1” and at 6 months “T6,” the latter being exploratory). All data, including LimeSurvey questionnaires, are hosted on servers at the University of Caen, France.

Randomization will be organized by placing 170 sealed opaques envelopes in which the participant’s group (control vs. experimental) will be specified. After completion of all measures in T0, participants select an envelope from a series of envelopes in a box at their disposal. The ignorance clause will hence be respected. The psychologists in charge of the interviews will be blind until the opening of the envelope drawn by the participant at the end of T0.

The inclusion phase incorporated the possibility of a substantial attrition rate (about 30%) to ensure sufficient statistical power. Therefore, trial exits (refusal to continue^1^, withdrawal of consent, or other) will not be replaced.

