### Study design and setting

All the study design and setting (see SPIRIT Checks in Additionnal File 1) has been elaborated by the trial steering committee (TSC) which is made up of the research team who authored this article, with the exception of Messrs [name] and [name], who were respectively responsible for the development and design of the ALCOODUC mobile app. The TSC, comprising nine people, is made up of academics specializing in prevention issues and field experts specializing in alcohol-related problems and/or the practice of mindfulness meditation. This steering committee met on a monthly basis during the protocol design phase and validated each stage of the protocol submission process, notably at the level of the national ethics committee (see the “Ethics approval and consent to participate” section for a brief description of the French system).

This is a randomized controlled study in parallel groups. It will compare the monthly BD score between the control group and the experimental group, and the allocation ratio is 1:1.

One hundred seventy volunteer participants from the University of Caen (France) will be included in this research protocol (see Fig. 1). During the initial visit, after presentation of the study and signature of the consent form presented by one of the two psychologists in charge of the interviews, all participants will complete various online questionnaires (estimated completion time 40 min; LimeSurvey) as well as a screening for neuropsychological impairments using the BEARNI tool (Brief Evaluation of Alcohol-Related Neuropsychological Impairments [33]; estimated completion time of 20 min). Eighty-five participants will benefit from the control condition (i.e., a motivational interview), and 85 other participants will benefit from the experimental condition (i.e., a motivational interview associated with a mindfulness meditation session and intention implementation; estimated duration 1 h).

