### Statistical considerations

#### Power analysis

At an alpha risk of .05, the number of 120 subjects in total is sufficient to obtain a power greater than .80. This estimate is derived from a 3000 iteration Monte Carlo simulation based on a baseline of real data collected in November 2021 (*N* = 1917) with a Gamma distribution. In this simulation are parameterized an average decrease of 10% of the BD score in control group and an average decrease of 20% for the experimental group with an intra-subject variability (SD) linearly depending on the individual baseline (estimated to be ¼ of the baseline value + 0.5).

Considering a potential attrition rate of approximately 30%, 170 subjects will be included in the study at T0.

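### Free choice of a sealed envelope conceals the assignment before opening, but does not bind the participant to the envelope opened

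*Protocol article*

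**What the plan says.** The method is in the protocol article, Study design and setting (the text after Fig. 1). Randomization uses "170 sealed opaques envelopes in which the participant’s group (control vs. experimental) will be specified". The draw comes late in the inclusion visit: "After completion of all measures in T0". It is the participant who chooses: "participants select an envelope from a series of envelopes in a box at their disposal". The article then concludes: "The ignorance clause will hence be respected". On the staff it says: "The psychologists in charge of the interviews will be blind until the opening of the envelope drawn by the participant at the end of T0". That section also fixes two arms of 85 and states that "the allocation ratio is 1:1".

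Three other places bear on the point:

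- **Control group and Experimental group:** in both arms, the motivational interview is given by the psychologist who received the participant for inclusion.
- **Trial status:** recruitment was still open at publication, with 98 of 170 included.
- **Study objectives:** the outcome is self-reported by participants through a mobile application.

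**The concern.** Allocation needs two protections. Nobody should be able to foresee the assignment before the participant is committed, and once revealed it should be the one that is used. Sealing and opacity give the first. The second needs a link, made before opening, between a particular envelope and a particular participant. A free pick from a box makes no such link.

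The setting makes this relevant. Participants are volunteers who have been told the study's objectives (Recruitment of participants and material; Procedure and measures). The person in the room at opening is also the person who goes on to treat. If a participant disappointed by the slip were allowed another pick, the arms would no longer be formed by chance alone, and the comparison of a self-reported outcome would carry that selection. The baseline comparison in Data management and analysis plan covers age, sex, AUDIT, trait anxiety and depression. Readiness to change is not among them, so selection on motivation would not be examined at that step.

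**Working it through.** **Inputs.** 170 envelopes for 170 participants, 85 per arm (Study design and setting); 98 included (Trial status); 120 evaluable and about 30% attrition (Power analysis).

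**Step 1: the envelope count.** 120 / (1 − 0.30) = 171.4, or 172 rounded up. Conversely, 170 × 0.70 = 119. The stated 170 agrees with the inputs to within rounding. There is one envelope per planned participant and no spare, and the article says that exits are not replaced.

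**Step 2: what a count can detect.** With 98 participants allocated, 170 − 98 = 72 sealed envelopes should remain.

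| Event after opening | Used + remaining | Visible on a count? |
|---|---|---|
| k envelopes discarded | 98 + (72 − k) = 170 − k | Yes, a shortfall of k |
| Envelope resealed and returned, another drawn | 98 + 72 = 170 | No |
| Envelopes swapped between participants | 98 + 72 = 170 | No |

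If all k discarded envelopes were control, the experimental share of those left is 85 / (170 − k):

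- k = 1: 85/169 = 50.3%
- k = 5: 85/165 = 51.5%
- k = 10: 85/160 = 53.1%

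With resealing or swapping, the final totals stay at 85 and 85.

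**Step 3: what the arm split can detect.** For an honest draw of 98 from 85 + 85, the number in the experimental arm is hypergeometric:

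- mean = 98 × 85/170 = 49
- variance = 98 × 0.5 × 0.5 × (170 − 98)/(170 − 1) = 24.5 × 72/169 = 10.44
- SD = 3.23, with a 95% range of 43 to 55

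The interim arm split is therefore a blunt check. It does not replace the envelope count, and it says nothing about how many re-draws occurred.

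**Step 4: the stated conclusion against the stated procedure.** Sealed opaque envelopes, drawn after the T0 measures by the participant, support concealment up to opening. The text on the psychologists' blinding ends at that same moment. From opening onward, the article describes no step that makes the drawn assignment binding. The word hence in the concealment sentence is justified for the period before opening only.

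**The case against.** The strongest reply has four parts.

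- **The pick is blind.** This stands. The group is inside a sealed opaque envelope, the draw follows consent and all T0 measures, and a free draw stops anyone reserving the next assignment. Exchanging one unopened envelope for another does no harm.
- **A discarded envelope is detectable.** This stands too. With exactly 170 envelopes, a count would show it. Only resealing or swapping escapes, and resealing a sealed envelope takes some effort.
- **A journal article leaves numbering, custody and logs to the full protocol.** This stands in part. A log, or a rule to keep opened envelopes, may exist in material not shown, and its absence here is not a fault. But the article itself fixes the method of selection. A fixed order of use would contradict a free choice by the participant, not complete it.
- **The Discussion's remarks on motivation concern the wish to reduce drinking, not a preference for the mindfulness arm.** This is fair, so the direction of any selection is a plausible supposition and not something the article states.

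A reader might also infer that controls are told outright that they are the comparator, and that this biases their self-report. The article does not give the wording on the slip, who reads it or how it is explained. In any case, participants cannot be blinded to whether they had a meditation session.

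**Conclusion.** The point holds in a limited form. The stated procedure conceals the assignment until opening. It does not secure adherence to the assignment drawn, and the concealment sentence claims no more than the first if read strictly. A re-draw by resealing or swapping could not be detected under the method described; a discard could, provided the 170 are reconciled.

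The effect on the treatment comparison cannot be quantified from the article. The 43 to 55 range describes how weak the arm split is as a check and is not an estimate of bias. It would go too far to conclude that irregular allocation leaves no trace whatever, or that the allocation was subverted: the fixed envelope count contradicts the first, and nothing in the article supports the second.

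The verdict assumes that the article describes the draw as it is carried out, and that the full protocol adds no safeguard that links envelope to participant before opening. This is a worthwhile, low-cost improvement and not a fault that invalidates the design.

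**What to change.** **For the remaining places** (170 − 98 = 72 at the reported status, fewer if recruitment has moved on):

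1. Have someone who does not run visits prepare envelopes numbered in the order of a computer-generated list. The list should hold the assignments still needed to reach 85 and 85.
2. Use them strictly in number order.
3. Write the participant code and date on the sealed envelope before it is opened.
4. Keep every opened envelope, and at the end check number order against inclusion date.

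**For the draws already made:** count used plus remaining envelopes, compare the total with 170, and report the result, including any shortfall. State that this check cannot exclude resealing or swapping.

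**In the text:** limit the concealment sentence to the period before opening, and describe the change of method and the date it took effect.

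The cost is minor clerical work. No extra visit is needed, and the sample size and analysis do not change. The draws already made stay under the old method. Neutral slip wording (A or B) is optional; it may soften the effect of the word control, but it does not blind anyone. Comparing the treatment effect before and after the change is not worthwhile: 98 × 0.70 ≈ 69 against 72 × 0.70 ≈ 50 evaluable participants, when the full 120 was sized only for the main contrast.

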### Eligibility criteria

To be eligible, subjects must meet all the defined inclusion criteria. The population, made up of students who consume alcohol recruited within the University of Caen, will be aged between 18 and 30 years, French native speaker, of both sexes, with a binge drinking score^2^ > 1, having signed an informed consent. In addition, subjects meeting any of the following exclusion criteria will not be eligible to participate in the research: pregnant or breastfeeding students, students reporting a history of neurological, neurosurgical, psychiatric or endocrine disease, or infectious disease.

### Recruitment of participants and material

Participation in the study will be proposed to all students of the University of Caen through their institutional email address. In this email, the study will be briefly presented and a link to a LimeSurvey questionnaire will be proposed. On this link, the research and its objectives will be presented in more details, followed by questions on the elements of inclusion and exclusion.

Based on their responses, volunteers may or may not be included in the study sample. An email will inform them of this decision and the volunteers who meet the inclusion criteria will be invited to contact one of the investigating psychologists to schedule the inclusion visit.

### Procedure and measures

After the online pre-inclusion screening, the inclusion visit will be organized in person (see Fig. 2 for the SPIRIT timeline requirements contents). During this visit, the investigating psychologist will remind the participant of the research and its objectives, will provide the information letter on the foreseeable risks and constraints of the trial, and will collect the participant’s informed consent. An anonymous email address will be created to allow participants to contact their referring psychologist in case of need and to send the data recorded in the mobile application while maintaining their anonymity. This inclusion visit also includes the presentation of the ALCOODUC mobile application allowing all participants to regularly record their alcohol consumption and its modalities during the next 6 months and for the participants of the experimental condition to record their MBM-based practice rhythm as well as the programming of subsequent solicitations. The details of the questions integrated in the mobile application are available on osf: https://osf.io/3n4c6/.

**Fig. 2 Fig2:**
[figure not shown]
Schedule of enrolment, interventions, and assessments. NB: T1 (+ 1 month). T6 (+ 6 months). MI, motivational interviewing; MBM, mindfulness-based meditation; II, implementation intention

During the first experimental period (T0), both a screening for neuropsychological disorders and an online questionnaire including various psychological measures^3^ will be proposed.

A screening for *neuropsychological disorders* will be offered to all participants using the BEARNI tool (Brief Evaluation of Alcohol-Related Neuropsychological Impairments [33]). BEARNI was specifically designed to screen for cognitive and motor deficits in individuals with alcohol use disorders, including deficits in episodic memory, working memory, executive functions, visuospatial abilities, and ataxia. It contains five subtests: a verbal episodic memory subtest (maximum score: 6 points), an alphabetic span subtest assessing verbal working memory (maximum score: 5 points), an alternating verbal fluency subtest assessing flexibility abilities (maximum score: 6 points), a five complex figures subtest assessing visuospatial abilities (maximum score: 5 points), and an ataxia subtest assessing balance (maximum score: 8 points). The BEARNI tool provides six scores: five sub-scores (one for each of the sub-tests) and a total score (maximum score: 30 points).

#### Socio-demographic data

Information on age, sex, height, weight, and academic year will be collected.

#### Alcohol consumption

Information on age of onset, number of drinks per week (weekly alcohol consumption (WAC)), and type of alcohol will be collected.

#### Binge drinking practices

As indicated earlier, BD score [34] is calculated on the basis of three distinct elements (Q1: “number of average standard drinks per hour (containing about 10g of pure alcohol in France)”; Q2: “number of drunken episodes in the year”; and Q3: “percentage of drunken episodes among the occasions of drinking”). The score results from the following weighting: (4 × Q1) + Q2/2 + (0.2 × Q3). This score considers both the quantity and frequency of drinking, thus integrating the dimension of repeated alcohol withdrawal. To note, the index will need modification to measure BD practice at 1 month and 6 months after the program. Specifically, at T1 (+ 1 month), the BD score will be based on a 1-month-based Q2: “number of episodes of drunkenness in the last month” which will consequently modify the formula (4 × Q1) + Q2 × 6 + (0.2 × Q3). At T6 (+ 6 month), the BD score will be based on a 6-month-based Q2: “number of drunken episodes in the last 6 months” which will consequently modify the formula (4 × Q1) + Q2 + (0.2 × Q3).

#### Risk of alcohol dependence

AUDIT Questionnaire (Alcohol Use Disorders Identification Test) is a 10-question measure designed to identify people who are at risk of developing alcohol-related problems or who are actually experiencing such problems [35]. The AUDIT has been validated and recommended as an effective measure for alcohol among students [36].

#### Craving

One item was included to check the possible craving frequency episodes experienced by the participant.

#### Use of substances other than alcohol

For each other substance (tobacco, cannabis, ecstasy/MDMA, amphetamines, cocaine, heroin, new synthetic drugs excluding ecstasy), participants will be asked to provide a binary response regarding their use (no vs. yes).

#### Impulsivity

Impulsivity is measured using the French version of the short UPPS scale assessing five facets of impulsivity [37]: Negative vs. Positive Urgency (i.e., the tendency to act rashly to regulate a negative vs. positive emotion), Lack of Premeditation (i.e., the tendency to favor immediate reward options without considering the potential consequences of the action), Lack of Perseverance (i.e., poorer concentration on boring or difficult tasks and increased distraction), and Sensation Seeking (i.e., the tendency to seek a new or exciting experience). Participants are asked to respond to 20 statements on a Likert scale from 1 = strongly agree to 4 = strongly disagree.

#### Anxiety

Anxiety is assessed using the French version of the State-Trait Anxiety Inventory (STAI [38]). It consists of 20 items ranging from 1 = no to 4 = yes.

#### Depression

Depressive symptoms are assessed using the French version of the Beck Depression Inventory (BDI-13 [38]). It consists of 13 items (*α* = .87) each composed of four statements reflecting varying degrees of severity of the depression symptom.

#### Mindfulness

The Five Facets Mindfulness Questionnaire (FFMQ [39, 40]) is a 39-item measure of a person’s level of dispositional mindfulness (i.e., personality trait). Participants are asked to respond on a scale ranging from 1 = never or very rarely true to 5 = very often or always true. The FFMQ includes 5 subscales: observation (8 items), description (8 items), acting consciously (8 items), non-judgmental (8 items), non-reactivity (7 items). The sum of the 39 items assesses overall dispositional mindfulness.

#### Motivation to stop/regulate drinking (Readiness to Change-Alcohol, RTC-Alcohol)

In order to evaluate the participants’ readiness to change in their behavior towards alcohol, we will administer the RTC-Alcohol questionnaire to all the students included in the study. This self-assessment based on the transtheoretical model of behavior change [37, 38] is recognized for its reliability and validity. The RTC-Alcohol has three different scales that correspond to an assessment of the three main stages of behavioral change: the pre-contemplation, contemplation, and action stages. Based on the person’s score on each of these scales, the experimenter determines which stage of behavior change the person is in.

#### Motivation to use mindfulness meditation (RTC-Meditation)

In order to assess participants’ behavioral changes regarding the practice of mindfulness meditation, we will offer the RTC-Meditation questionnaire (based on the RTC-Alcohol) to all students included in the study.

Once the neuropsychological evaluation and all the questionnaires have been completed (estimated duration 50 min), on the basis of a random assignment (see randomization procedure with envelopes), the participant will be integrated into the control group or the experimental group. Regardless of the group, all participants will participate to a motivational interviewing session. Only the experimental group will participate in a mindfulness meditation session associated with an implementation intention session.

### Interventions

Distinct interventions are proposed according the allocated group. The framework trial is to test the superiority of the intervention proposed in the experimental group compared to the intervention proposed in the control group.

#### Control group

Participants in the control group will receive no specific psycho-social intervention except that they will benefit from a motivational interview with the psychologist who welcomed them for inclusion.

#### Experimental group

Similar to the control group, participants will benefit from a motivational interview with the psychologist who welcomed them for inclusion. Yet, this motivational interview will be completed by two activities: mindfulness-based initiation and implementation intention exercises.

The mindfulness meditation session is structured in four steps. The session begins with the meditation called “grape exercise” associated with the “sound meditation.” In a second step, the principles of mindfulness meditation (conceptualization of MBM, autopilot and acceptance) are explained to the participants by the psychologist. The session continues with two exercises, the first named “Sitting Meditation Space on thoughts” and the second “SOBER Breathing Space in the face of 1 Challenge situation.” At the end of the session, an explanation on the memo sheet available on the mobile application is given to the participants so that they can continue their practice if a risky substance use situation arises.

The implementation intention session follows the MBM initiation. It focuses on the implementation of two behaviors, on the one hand, regular MBM-based training (II-1) and, on the other hand, the use of MBM in risky drinking situations (II-2). The two systematic phases related to an II process are specific to each of the two implementations (all details available on osf: https://osf.io/3n4c6/.

II-1 deals with the implementation of a daily and/or regular use of MBM. It focuses first on the identification by the participant of a situation, in terms of place, moment of day, and context, which represents an opportunity to reach the goal of practicing MBM on a regular basis, or an obstacle to reaching this goal (II-1a). Then, the participant is invited to identify a thought or behavior that is relevant, for him or her and in this situation that he or she has chosen, to seize this opportunity or overcome this obstacle (II-1b). On this basis, the participant is invited to explicitly formulate the link between these two elements in the linguistic format “If (II-1a), then (II-1b),” to copy it once, to repeat it quietly in his/her head 3 times while trying to represent the scene concretely. The participant must repeat the exercise a second time by proposing another “II-1a” and another “II-1b.”

The II-2 on the implementation of the use of MBM in risky situations is structured in the same way. First, the participant is asked to identify a situation, in terms of location, time of day, or context, that represents an opportunity to achieve the goal of regulating one’s drinking with the help of the MBM or an obstacle to achieving this goal (II-2a). The participant is then asked to identify a thought or behavior that is relevant to him or her in the situation he or she has chosen, in order to seize this opportunity or overcome this obstacle (II-2a). On this basis, the participant is invited to explicitly formulate the link between these two elements in the linguistic format “If (II-1a), then (II-1b),” to copy it once, to repeat it quietly in his/her head 3 times while trying to represent the scene concretely. The participant must repeat the exercise a second time by proposing another “II-2a” and another “II-2b.”

